### Objectives

Our objective is to study whether the integration of APNs in the primary care of multimorbid patients leads to optimized care of the target group and to a reduction in the workload of the GPs. Improved care is expected to be reflected by a stabilization of the patients' health and home care situation. This will be expressed as the reduced use of emergency contacts (emergency services, emergency room, acute inpatient admission) and GP visits, thus reducing overall treatment costs. Finally, we expect to observe high satisfaction from all parties involved (physicians, patients, relatives, ANPs and medical assistants) with this type of care.

### Trial design

The FAMOUS trial is a prospective multicentre mixed methods study. Patients with at least three chronic conditions across nine participating general practices are eligible to be treated as an intervention group by a trained APN. All patients will be treated by APNs for twelve months. Data on the period of intervention are available as data from health insurance companies or the Association of Statutory Health Insurance Physicians (ASHIP) or data collected by the APN. The intervention group will be compared with a control group of patients from German health insurance who are matched according to age, sex, comorbidity and living in a nursing home. The matching will be performed at a ratio of one FAMOUS patient to two control patients.

Qualitative interviews will take place with GPs, APNs and patients to assess factors that are difficult to capture using quantitative data. This evaluation procedure will be carried out by an independent institution (IMBEI). In addition, the intervention will be assessed in more detail in an internal evaluation from the trial sponsor using a longitudinal design.

## Methods: participants, interventions and outcomes

### Study setting

The study is being conducted in nine general practices in rural areas of Rhineland-Palatinate, Germany. GPs interested in participating in the study were invited to apply and were selected by the project team of Catholic University of Applied Sciences (CUAS). The main criteria for selection were the number of suitable multimorbid patients and the willingness of the practice to implement the intervention. The number of treatment cases in the participating general practices ranges between 2000 and 6000 patients per quarter. Approximately 30% of them are multimorbid. With the size of the practice, we have ensured that the number of potentially eligible patients is sufficient to achieve the number of cases targeted in the study.

### Eligibility criteria

Patients (or a legal representative) must provide written informed consent before any study procedures occur. The inclusion criteria are as follows: at least 18 years of age; medical diagnosis of at least three chronic diseases that have led to GP treatment in at least three out of four quarters in the last twelve months; and insured by statutory health insurance. The exclusion criterion is a life expectancy less than 12 months as assessed by the treating physician.

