	Key inclusion and exclusion criteria	Gender: all genders Minimum age: ≥ 18 years Maximum age: no maximum age Further inclusion criteria: medical diagnosis of at least three chronic diseases, which in the past 12 months in at least three out of four quarters have given rise to general practitioners’ treatment;being in general practitioners’ treatment; insurance with a statutory health insurance company. Exclusion criteria: not fulfilling the inclusion criteria; being in the dying phase according to the assessment of the general practitioner.
	Study type	Interventional, nonrandomized, nonblinded controlled trial
	Date of first enrolment	2021/10/01
	Target sample size	*n*=2451
	Recruitment status	Recruiting
	Primary outcome(s)	Number of emergency contacts
	Key secondary outcomes	Use of other health care facilities (e.g. hospital, nursing home), hospital readmission and visits by general practitioners
3 Protocol version	Issue Date: 2021/10/01	
4 Funding	There was financial support only, provided by the German Innovation Fund of the Federal Joint Committee. The Innovation Fund uses funds from the statutory health insurance (SHI) to support innovative, cross-sectoral new forms of care and patient-oriented care research projects in order to further develop and improve SHI-financed care in Germany	
5a Author details	RS and EG initiated the study design; CDS is responsible for the project management; JK developed the concept of the internal evaluation and will conduct it. EG and MB developed the concept of the external evaluation; BB and MB together with a statistician are planning and will conduct the statistical analysis. BB is responsible for the implementation of the qualitative interviews. All authors contributed to the development and refinement of the study protocol and approved the final manuscript.	
5b Name and contact information for the trial sponsor	Trial Sponsor: Catholic University of Applied Sciences Mainz (CUAS) Contact name: [name]. [name] Address: [name], Germany Telephone: [name] Email: [contact]	
5c Role of funder	This funding source had no role in the design of this study and will not have any role during its execution, analyses, interpretation of the data, or decision to submit results.	

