### Outcomes

#### Primary endpoint

The primary endpoint is the number of emergency contacts per patient within one year. Emergency contacts are visits to the on-call medical service, GP contacts outside office hours and unplanned hospital admissions.

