### Recruitment

Recruitment of patients will be carried out by the participating general practitioners through a direct approach. Patients trust their GPs, so a recommendation to participate made by primary care physicians is likely to result in a high participation rate. The recruitment process is supported by the offer of personal contact between APNs and potential participants in the enrolment phase. In addition, to support recruitment, the patients are provided with comprehensive information and educational material about the project in easy-to-understand language, informing them about the project, its objectives and the data collection and processing that will be carried out to achieve the project goals. Posters and flyers are placed in the waiting rooms of the participating GP offices and are customized with the individual data of the general practice and the APN.

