## Methods: data collection, management, analysis

### Data collection methods

For the independent evaluation, data from ASHIP and the health insurance fund will be used for primary and secondary endpoints. To fill in missing data, such as hospital visits for patients with other health insurance, APNs collect health-related data and document patients' emergency and routine visits to any health-related facility (doctor's office, hospital, emergency room). The health insurer provides a data pool for control group matching. All data are transferred to the IMBEI in pseudonymized form. Patients, GPs, and APNs are informed by mailed invitations about the possibility of interview participation and asked to complete a feedback form. Potential interviewees are called via the feedback form, and appointments are made. The qualitative interviews are conducted by telephone using a previously prepared standardized interview guide. There is a separate guide for each interview group, which is finalized after piloting. Interviews are audio recorded and transcribed verbatim.

As part of the internal evaluation, the health status of each participating patient was measured before (t0) and at the end of the patient-individual intervention phase (t1) using the assessment instruments mentioned in the intervention section above as we use the data from these instruments for care and research purposes. Their psychometric data are as follows: DemTect: interrater reliability *r* = 0.993, sensitivity 85.1%, specificity 97% [14]; MNA: internal consistency α = 0.701, test–retest reliability *r* = 0.697 [23]; NRS: with a cut-off point NRS > 4, the sensitivity of ‘unbearable pain’ is 83%, while the specificity is 96.7%, with a cut-off point NRS > 5, the sensitivity is 94%, while the specificity is 85% [24]; PDI: internal consistency α = 0.86, [17]; HAQ: internal consistency α = 0.78–0.98 [25, 26]. The psychometric results of the German translation are as follows: test–retest reliability 0.94, internal consistency α = 0.92, criterion validity 0.76 [27]; MILVA: internal consistency range between α = 0.61–0.94, sensitivity 72%, specificity 59%; [17]. PAINAD-G: internal consistency α = 0.85, interrater stability *r* = 0.80, retest reliability* r* = 0.90 [21]; DEMMI: internal consistency α = 0.83, interrater reliability ICC 0.94 [28].

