### Statistical and further methods

#### Statistical and further methods for primary and secondary outcomes

Statistical analyses of the independent evaluation take place as a comparison between intervention and control groups. Poisson regression will be used for both the primary and secondary endpoints. Adjustments are made for relevant confounders but not for matching variables. APN practices in the intervention group are not considered clusters because a comparable cluster variable is not available for the control group.

Users of the new form of care (patients, participating primary care physicians, and APNs) will be interviewed in qualitative interviews. The interviews will take place at the end of the intervention period to reflect the experiences made. Additionally, primary care physicians will be interviewed at the beginning of the project to map expectations of the new form of care. It can be assumed that a theoretical saturation – i.e., the point at which new interviews no longer provide additional information – will be reached with *n* = 5 GPs and *n* = 5 APNs. Full data collection from all 9 practices participating in the project will nevertheless be targeted. For patients, a number of *n* = 30 participants is expected to reach theoretical saturation.

Cost analysis from the social health insurance perspective will be performed to evaluate potential savings. Costs will be compared between the intervention and the control group. Total cost analysis and cost analysis within subgroups will be carried out to identify areas with the highest costs or cost savings. These subgroups will be identified through the primary and secondary endpoints. Data for the health economic analysis will be obtained from the participating health insurance. Intangible or nonmedical costs will not be analysed since these data are not available in the insurance dataset.

In the internal evaluation, descriptive and analytical statistical methods are used. The patient’s situation at the beginning and at the end of the APN intervention and the nursing process will be described by statistical indicators such as percentual distribution, mean and standard deviation or median and quartile deviation. Depending on the kind of data and on its distribution, parametric or nonparametric statistical analyses will be conducted (e.g., variance analysis, t test, Mann-Whitney U test or Wilcoxon test).

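### The exclusion criterion is stated in two conflicting ways and rests on a physician's judgement not described for controls, so patients near the end of life may be over-represented in the control group

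*Protocol article*

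**What the plan says.** The article gives the exclusion criterion twice.

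- Eligibility criteria: "The exclusion criterion is a life expectancy less than 12 months as assessed by the treating physician".
- Table 1 (Administrative information, key inclusion and exclusion criteria): "being in the dying phase according to the assessment of the general practitioner".

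The intervention group is screened in the practices: "Recruitment of patients will be carried out by the participating general practitioners through a direct approach". Controls arise differently. Under Data collection methods, "The health insurer provides a data pool for control group matching", and Trial design describes "a control group of patients from German health insurance who are matched according to age, sex, comorbidity and living in a nursing home".

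On analysis, the statistical methods section says: "Adjustments are made for relevant confounders but not for matching variables". The confounders are not named. The outcome at stake is defined under Primary endpoint: "The primary endpoint is the number of emergency contacts per patient within one year". It includes unplanned hospital admissions. The Sample size section plans for a reduction from 2.7 to 2.295 contacts per patient and year.

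**The concern.** There are two linked problems.

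The first is a contradiction. A patient expected to live nine months, but not yet dying, is eligible under Table 1 and ineligible under the eligibility section. Both statements are current text. As the article stands, GPs in nine practices could recruit to different rules.

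The second is an asymmetry between the groups. Either wording requires a physician to judge an individual's prognosis at recruitment. The article describes no such assessment for a control drawn from insurer data and no routine-data substitute for it. Age, sex, comorbidity and nursing-home residence are related to prognosis but do not measure it. In a non-randomised comparison that relies on matching to limit confounding, the two groups are therefore screened differently on something plausibly related to the primary count. Part of an observed difference in emergency contacts could then reflect who was allowed into each group and not the nurses' care.

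**Working it through.** **The plan's own effect.** 2.295 / 2.7 = 0.85, the stated 15% reduction. This is the yardstick for any bias.

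**Assumed inputs (neither is in the article).** q is the excess share of end-of-life patients among controls. k is their rate of emergency contacts relative to other patients while alive. All other patients have relative rate 1, and the true intervention effect is nil.

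**Three ways to count exposure.**

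1. Full year for everyone: ratio = 1 / (1 + q(k − 1)).
2. End-of-life controls contribute half a year on average (assumption), raw counts per patient: ratio = 1 / (1 − q + 0.5qk).
3. The same half year, analysed with a person-time offset: ratio = (1 − 0.5q) / (1 − q + 0.5qk).

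**Worked case, q = 5%, k = 3.**

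- Full year: 1 / 1.10 = 0.909.
- Half year, counts: 0.95 + 0.05 × 0.5 × 3 = 1.025, and 1 / 1.025 = 0.976.
- Half year, offset: person-time is 0.95 + 0.05 × 0.5 = 0.975, and 0.975 / 1.025 = 0.951.

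**Range.**

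| q | k | Full year | Half year, offset | Half year, counts |
|---|---|---|---|---|
| 3% | 2 | 0.971 | 0.985 / 1.000 = 0.985 | 1.000 |
| 5% | 3 | 0.909 | 0.951 | 0.976 |
| 10% | 4 | 0.769 | 0.95 / 1.10 = 0.864 | 1 / 1.10 = 0.909 |

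With full-year exposure, the whole planned effect would appear without any true effect if q(k − 1) = 1/0.85 − 1 = 0.176.

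**Imperfect prognosis.** Suppose physicians recognise only half of a 5% group. The intervention group then keeps 0.025 / 0.975 = 2.56% of such patients. On half-year counts with k = 3, its mean is 0.9744 + 0.0256 × 1.5 = 1.013, and 1.013 / 1.025 is about 0.99.

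**Direction.** On raw counts with half a year of exposure, the bias vanishes at k = 2, because 0.5 × 2 = 1. Below k = 2 it runs against the intervention.

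**Which wording.** Under Table 1 only the dying phase is screened out, so patients in their last year who are not yet dying can enter both groups. That makes q smaller than under the 12-month wording. The article gives no figure for either.

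**The case against.** A reader might infer that end-of-life patients remain in the control group only, and that this produces a spurious reduction of about 9%. The documents support neither statement. Exclusive presence among controls would require the 12-month wording and perfect prognosis. It fails under the Table 1 wording, and matching on age, comorbidity and nursing home removes part of any difference. The 9% figure gives every such control a full year of exposure at three times the rate, although patients in their last year die during follow-up.

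It can also be said that an article does not normally spell out how a claims-based control pool is filtered. A substitute rule may sit in the full protocol or analysis plan. Adjustment for relevant confounders and sensitivity analyses are both announced. Finally, higher emergency use near death is an assumption with no source in the article, so the direction of bias is not fixed by the text.

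These points stand, and they limit the size and the certainty of the bias. They do not remove the contradiction between the two sections. Nor do they alter the fact that, as described, a physician's judgement screens one group and the matching variables do not reproduce it. Unnamed confounders and unspecified sensitivity analyses cannot be credited with closing that gap.

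**Conclusion.** The conflict between Table 1 and the eligibility section is certain. The difference in screening is real as the article is written. Over-representation of end-of-life patients among controls is a plausible consequence, not an established one.

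If those patients accrue more emergency contacts, the ratio is biased toward benefit. At an assumed 5% excess share and three times the rate, a null effect would show about 0.91, 0.95 or 0.98, depending on how exposure is handled. That is roughly 9%, 5% or 2% against a planned 15%. The first figure is close to an upper bound for its own inputs. The bias shrinks further under the Table 1 wording or with incomplete recognition by physicians. The article supplies neither the share nor the rate, so no single figure should be reported as the expected bias.

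**What to change.** 1. Reconcile Table 1 with the eligibility section so that one exclusion criterion is stated. Which one is a clinical matter for the investigators and is not decided here.
2. Define one end-of-life indicator from look-back routine outpatient billing data, for example palliative-care billing. Apply it identically to intervention patients and controls at the index date for the primary comparison. The section on analysis population and missing data says that outpatient data from the physicians' association are available for all patients. It should be confirmed that the extract covers the look-back quarters.
3. Do not exclude controls because they die during follow-up. That would select on a later event and introduce a new bias.
4. Pre-specify a sensitivity analysis that drops the last months before death in both groups. The article already foresees sensitivity analyses.

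Matching additionally on prior-year hospital days or care level is not proposed. The article describes no pre-enrolment inpatient source for patients of other insurers, and it does not mention care level.

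The cost is one consistent sentence, one filter run on both groups and one further analysis. A few enrolled patients may leave the primary analysis set. Some asymmetry remains for patients near the end of life who carry no such codes, because the physician's screen still acts on the intervention group alone. That should be stated as a limitation.

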### Interventions

#### Intervention description

The intervention aims to integrate person-centred and evidence-based APN care for multimorbid patients in general practices in rural areas in Germany. To be eligible for participation, the general practice must confirm its willingness to change some structural and process routines to integrate APN work into its workflow. Examples include providing a treatment room and a car for home visits as well as ensuring weekly case conferences to support APN work.

The qualification profile of APNs includes a professional nursing licence, at least two years of professional experience in nursing and an academic degree at the master’s level in a nursing-related program. In addition, APNs complete 500 h of project-specific training.

Within the scope of the study, APNs take over the care of multimorbid patients. The integration of APN care for multimorbid patients in practice is a complex intervention [13]. The complexity arises for various reasons. First, multimorbidity is defined by the number of diseases without further delineation, which means that the diseases and their combinations can vary greatly from one individual to another. The varying care needs lead to individual care goals. To achieve these different goals, APNs must take on a number of possible roles depending on the needs of the patients, and their activities must be selected and implemented flexibly.

To stabilize the individual health care situation, APNs implement the care process, establish or improve a supportive network and intensify the communication between all those involved in the provision of care. Furthermore, APNs actively involve patients in the care process and specifically promote patient autonomy. Conducting the care process means developing, carrying out, monitoring and evaluating a person-centred and evidence-based care plan.

APNs generally begin the care process with an in-depth assessment of cognitive capabilities, nutritional status, pain status, mobility status and psychosocial status. In the first step, cognitive performance is checked with a Dementia Detection test (DemTect) [14]. Depending on the result, different instruments or different data sources are used. If the DemTect score is above eight points, the following instruments are used: The Mini Nutritional Assessment (MNA) [15], Numeric Rating Scale (NRS) [16], Pain Disability Index (PDI) [17], Health Assessment Questionnaire (HAQ) [18], and Mannheim Inventory of Living Conditions in Old Age [Mannheimer Inventar der Lebensverhältnisse im Alter (MILVA)] [19]. In such cases, the data source is represented by the self-statements of the patients. If the DemTect score is less than or equal to eight points, the MNA and MILVA are still used but are assessed based on third-party observation, mainly by relatives. To measure the presence or extent of pain in this group, we use the Pain Assessment in Advanced Dementia Scale (PAINAD-G) [20, 21]. The De Morton Mobility Index (DEMMI) [22] is used to assess mobility. In addition, a clinical assessment is performed. Based on the values of the assessment instruments and the clinical assessment, a needs assessment is prepared, which forms the basis for the care plan. Taking the patient's individual needs and requirements into account, APNs plan specific interventions together with the patients and their relatives, as appropriate, to improve the patient's overall health and autonomy. In doing so, they implement the principle of shared decision-making. The interventions of the care plan are aimed at stabilizing or improving physical health, such as mobility, nutrition, neuropsychiatric state, continence status, skin condition/wounds, pain status and medication management, psychosocial situation, self-management skills, home living situation and social situation around loneliness. Where possible, the APNs involve family members and other related parties in the provision of care. In addition, the APNs include other stakeholders from the health care sector, such as outpatient care services, care advice centres, physiotherapists, and occupational therapists, or initiate further support services, such as volunteer visitation services or citizens’ buses.

The initial assessment takes place in the patient's home. Depending on the patient's condition, this initial examination is performed over one or two visits. Due to the patient’s condition and to his or her often reduced mobility, most of the follow-up visits also take place in the patient’s home. If possible, patients are seen at the APN consultation hours, which is held in the rooms of the GP ‘s office. All patients receive a business card with the APN's contact information so they can contact them by phone or email between scheduled visits if needed.

Weekly case conferences are scheduled for consultations with the GP. If necessary, short-term consultations are possible at any time. In the regular case conferences, APNs and GPs discuss the health status and the care situation of the participating patients. APNs make suggestions for further treatments, while the GPs decide on the medical procedure. Following German law, the medical side of care is provided under the delegation model.

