## Abstract

**Background:**

Multimorbidity is a common phenomenon among patients treated in general practices. Key challenges within this group include functional difficulties, polypharmacy, treatment burden, fragmentation of care, reduced quality of life and increased health care utilization. These problems cannot be solved in the short consultation time of a general practitioner (GP) since there is an increasing shortage of GPs. In many countries, advanced practice nurses (APNs) are successfully integrated into primary health care for multimorbid patients.

The objective of this study is to examine whether the integration of APNs in the primary care of multimorbid patients in Germany leads to optimized care of the target group and to a reduction in the workload of the GPs.

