#### Adherence

The introduction of APN roles and APN care in primary care practices is new for everyone involved. Including APNs, primary care physicians and patients. The primary burden for this implementation process falls on APNs, but physicians are also involved. Therefore, pioneer APNs are supervised by experienced mentors during their role development process in primary care. This mentoring consists of weekly short phone calls and monthly structured evaluation interviews. In addition, mentors conduct quarterly structured interviews with primary care physicians. Depending on the needs that become clear in the various conversations, supportive activities by the mentors can follow, with the aim of ensuring the implementation of the planned intervention.

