#### Secondary endpoints

The secondary endpoints in question are the use of continuing care institutions (inpatient hospitalizations, specialist visits, and nursing home stays), hospital readmission and home visits by primary care physicians. In addition, the expectations and experiences of participating physicians, APNs, and patients are mapped, and the financial impact of the intervention will be measured. The primary and secondary endpoints will be assessed by the IMBEI.

Outcomes of the internal evaluation are the health status of the patients and the satisfaction of physicians, patients and relatives with the APN care. In addition, the role development of the APNs and the experiences of the medical assistants are evaluated.

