### Auditing

The routine data provided by the health insurance company and ASHIP are controlled and quality-checked through well-established procedures. These high control standards are necessary beyond the research requirements because routine data are usually the basis for billing modalities.

The documentation form, which is used to document the patients' health status and the activities of the APNs, is continuously monitored by the experienced mentors who accompany the APNs. In the monthly structured evaluation meetings or - if necessary - in between, the mentors provide the APNs with feedback and discuss any need for improvement.

Mentors are part of the project team, which holds weekly meetings to discuss the progress of the project and to make steering decisions as necessary.

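### Lower GP workload is a stated aim, but only GP visits are compared with controls, and the GP time that the intervention adds is counted in no stated endpoint or analysis

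*Protocol article*

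**What the plan says.** **The aim.** The abstract and the Objectives section both ask whether integrating APNs "leads to optimized care of the target group and to a reduction in the workload of the GPs".

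**What is compared with controls.** The Objectives section says of the expected improvement: "This will be expressed as the reduced use of emergency contacts (emergency services, emergency room, acute inpatient admission) and GP visits". The abstract also names GP visits as an outcome. The registry data in Table 1 list "hospital readmission and visits by general practitioners" among the key secondary outcomes. The Secondary endpoints section narrows this to "hospital readmission and home visits by primary care physicians". None of these sections names GP time as an outcome.

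**What the intervention asks of GPs.** Practices must agree to hold weekly case conferences. The Intervention description adds: "Weekly case conferences are scheduled for consultations with the GP. If necessary, short-term consultations are possible at any time". GPs decide on medical treatment after hearing the APN's suggestions. Under Adherence, "mentors conduct quarterly structured interviews with primary care physicians".

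**Data sources.** Endpoints come from ASHIP and health insurance data. To fill gaps, APNs "document patients' emergency and routine visits to any health-related facility (doctor's office, hospital, emergency room"). The cost analysis uses insurer data. Under Auditing, a form covering patients' health status and "the activities of the APNs, is continuously monitored by the experienced mentors who accompany the APNs". GPs also complete questionnaires at the start and end, and give qualitative interviews.

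**The concern.** A visit count captures GP contacts that the APN may replace. It does not capture time the GP spends with the APN in conferences and short-notice consultations. That time is part of the intervention and arises only where there is an APN. If visits fall in the intervention group, readers may take this as an answer to the workload question when part of the GP's work has been left out of the sum.

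This matters because the article justifies the trial by the GP shortage and short consultation times, and plans to take its results to policy-makers. Whether APNs free GP time is one of the questions those readers will bring. The mismatch lies between an objective and the outcomes named to address it. It is not a detail of analysis that could be settled later: minutes never recorded cannot be recovered at the analysis stage.

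**Working it through.** The article gives no figure for GP time, so there is nothing to reproduce. The check sets the measures against the aim and then shows what the uncounted time could amount to.

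**Measures against the aim**

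| Source of information on GPs | Stated content | Control counterpart | Covers GP–APN time? |
|---|---|---|---|
| Routine data (ASHIP, insurer) | GP visits, or home visits only | Yes | Not stated |
| APN entries on utilisation | Patients' visits to facilities | No | Not stated |
| APN documentation form | Health status, APN activities | No | Possibly; fields not shown, no outcome uses it for GP time |
| GP questionnaires (t0, t1) | Satisfaction with APN care | No | Items not shown |
| GP interviews | Expectations and experiences | No | Not quantified |
| Cost analysis | Insurer data | Yes | Not stated |

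The only GP measure with a comparison is the visit count. Its definition also varies between sections; the home-visit version would leave out consultations in the practice as well.

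**Illustrative size**

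Inputs from the article: 817 intervention patients (Sample size), nine practices (Study setting), a consultation of under 10 minutes (Background and rationale), a weekly conference (Intervention description).

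Assumptions not in the article: conference length of 30, 60 or 120 minutes; one GP attending; 52 weeks per year; all patients of a practice under care at the same time.

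- Patients per practice: 817 / 9 = 90.8.
- GP minutes per patient-year = conference minutes × 52 / 90.8.
- Equivalent 10-minute consultations = GP minutes / 10.

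| Conference (min) | GP hours per practice-year | GP minutes per patient-year | Equivalent 10-minute consultations |
|---|---|---|---|
| 30 | 26 | 17.2 | 1.7 |
| 60 | 52 | 34.4 | 3.4 |
| 120 | 104 | 68.7 | 6.9 |

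Because a consultation is said to last less than 10 minutes, the last column is a lower bound for each row. Ad hoc consultations and any second GP attending would add to it.

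The number of patients under care at once also matters. The Data collection section refers to 24 months of project intervention, while each patient is treated for twelve. If patients came in two successive cohorts, about 817 / 18 = 45.4 would be under care at a time. The range would then be 34.4 to 137.5 minutes, or 3.4 to 13.7 consultations, per patient-year.

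**The case against.** The case on the other side has several sound parts.

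- *The article never says that workload will be judged by visits.* In the Objectives section the visit count is tied grammatically to improved care, and lower cost is the consequence named. This is right. But no other controlled measure bears on the workload aim, so the visit count is what a reader would use for it.
- *Visits are not the only information on GPs.* Questionnaires, interviews and mentor contacts exist, and their items are not shown, so it cannot be said that they omit workload. This stands. They still have no control counterpart, and workload is not their stated subject.
- *The APN form may already log conferences.* It may, since a conference is an APN activity. No stated outcome or analysis uses such entries, and if they exist the remedy is cheaper still.
- *The sizes are assumed.* They are. Conference length, attendance and concurrent patients are not given, and there is no baseline GP visit rate to set them against.
- *A net-time figure would mix measured minutes in one group with assumed visit lengths in both.* This is a fair reason not to rest the conclusion on such a figure.

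A reader might go further and infer that the visit measure is biased toward the aim by construction, or that total GP time will rise. The article does not support either. Visit counts also miss non-visit GP work that APNs may take over, such as coordination between providers, medication management and contact with relatives. The article also does not describe what billing data contain or how much non-visit work GPs do under standard care. The net direction is unknown.

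**Conclusion.** The concern holds as a mismatch between an aim and its measures. A change in GP visits, however defined, cannot by itself support a conclusion about GP workload here, because GP time added by the intervention is counted in no stated endpoint or analysis. The illustrative 17 to 69 GP minutes per patient-year shows that the omitted time need not be negligible. It rests on the stated assumptions about conference length, attendance and concurrent patients, and it is not an estimate of the net effect. The consequence is limited to the interpretation of a secondary aim; the primary endpoint, its sample size and its analysis are untouched.

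**What to change.** 1. In the existing APN documentation form, record the duration of, and GP attendance at, each case conference and ad hoc GP–APN consultation. If the form already holds this, extract it.
2. Report these GP minutes per patient-year for the intervention group, descriptively, next to the comparison of GP visits.
3. Use one definition of the GP visit endpoint throughout (all GP visits or home visits only), and describe the result as a result on visits. State that no workload reduction will be concluded from visit counts alone.
4. Optionally, show a net GP time figure as a sensitivity analysis, with the assumed time per visit stated and varied over a range.

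If the intervention is too far advanced for step 1, step 3 is the minimum.

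The cost is one or two form fields, a small documentation burden for the APNs and a workload picture that may look less favourable. Patient care and the primary analysis do not change.
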